#### Follow-up

Participants will be assessed at the same time points after being recruited in the study. Follow-up points for study participants translate into the following phases: baseline/pre-intervention, 6 months, and 12 months after baseline/pre-intervention. Table 4 shows data collection points.

### Data analysis

#### Descriptive summary of sample data

A description of participants' characteristics, including demographic information and baseline measurements, will be presented for both groups.

The entire cohort will also be summarised descriptively. For categorical data (smoking), frequencies and valid proportions and percentages will be used [48]. Numerical variables will be summarised using mean and standard deviation, or median and range or interquartile range. Risk ratios will be generated for selected outcome variables, dichotomised as necessary, from proportions of participants meeting particular criteria (e.g. control of blood pressure) in the control and intervention groups.

#### Primary outcome analysis (Quantitative and Qualitative data)

##### Objective 1: Feasibility

The proportion of those who showed interest in the study and are eligible to participate, agreed to participate, and those who remained in the study will be recorded. Percentages (%) of the number approached for participation will be used [48]. The average time to deliver the Intervention will be measured.

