### Primary outcomes

#### Feasibility

Feasibility will be ascertained by evaluating the recruitment and intervention processes. The study's feasibility requires that the Intervention be effectively carried out amongst an adequate number of first-degree relatives over 2 years. The assessment of the feasibility of the recruitment process will include records of the number of first-degree relatives:
Reached via patients/ video clip (link to video clip)/ poster (link to poster)/ study participants/ clinician,Who expressed interest in the study,Who are potentially eligible, with reasons for ineligibility,Who agreed to participate in the trial,Lost to follow-up (retention and drop-out rate),

Furthermore, the assessment of the feasibility of the Intervention will include the time taken to:
Complete the cardiovascular risk assessment,Deliver the Intervention (in-person session and telephone sessions).

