### Sampling frame

About seven acute coronary syndrome (ACS) patients are admitted to the acute general hospital per week, including unstable angina, non-ST and ST-segment elevation ACS. About 40% will present with premature ACS [4]. Maltese individuals who are 30 years and older often have quite extensive families. Across 52 weeks (1 year), logistically, if every patient informs their relatives, this would amount to over 100 eligible participants. Since there are no records concerning the recruitment uptake and attrition rate, we will dedicate two years for recruitment and data collection. A sample of 100 participants should be adequate to prove that the process is viable. As the pilot study is not expected to be powered to detect differences between groups, there is no universally accepted calculation for the pilot study sample size [38]. If a meaningful group difference is unknown and the pilot study is intended to establish an effect size for sample size calculation, it is recommended to have 30 to 40 participants recruited in each group. Recommendations for feasibility studies propose a minimum of 30 participants per arm to estimate parameters for future sample size calculations [39, 40]. Ultimately, the sample size decision for a pilot RCT must also consider the research timeline, human resources and costs, and the research objectives [40, 41].

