### Procedures

#### Recruitment

The flowchart displayed in Fig. 1 summarises the study design and participant flow, from enrolment to the final follow-up. Before discharge, all patients with acute coronary syndrome are enrolled in a hospital-based cardiac rehabilitation program. Patients with premature CHD, who attend cardiac rehabilitation, will be informed by their nurse about the study, which concerns their relatives. Patients will be the source of help to recruit study participants. Poster promotion of the study will be available at the cardiac rehabilitation reception area and local pharmacies. Poster and video clip promoting the study will be shared via the University's social media (Facebook, News point). Those having a sibling or a parent with premature CHD and are seeking cardiovascular risk assessment will be asked to answer a few questions via telephone to assess if they meet the inclusion criteria. Those found to be eligible will be invited for their baseline assessment at the hospital outpatient clinic.

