#### Recruitment method for interviews

All the intervention participants will be asked to complete a questionnaire at the end of the programme.

From a sample of first-degree relatives who completed the programme, 24 individuals will be asked to participate in the interviews. A stratified purposeful sample will be chosen varying on preselected parameters deemed analytically relevant to the Intervention, providing maximum variation. These are sex, age, and risk profile at 12 months. Participants for whom post-intervention outcomes did not improve and participants who had improved their risk profile at 12 months will be purposively selected for focused analysis to identify the Intervention's strengths and weaknesses [32].

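### Retention is expressed as a percentage of an undefined number approached, which mixes it with uptake, and the acceptability interviews are limited to programme completers

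*Protocol article*

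**What the plan says.** Feasibility and acceptability are the two primary objectives (Aim and objectives).

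**Feasibility.** Objective 1 under Primary outcome analysis names three groups: those interested and eligible, and then those who "agreed to participate, and those who remained in the study will be recorded". The next sentence supplies the only denominator: "Percentages (%) of the number approached for participation will be used". Under Primary outcomes, the Feasibility list of records starts with relatives "Reached via patients/ video clip (link to video clip)/ poster (link to poster)/ study participants/ clinician", followed by those "Who expressed interest in the study", those potentially eligible, those who agreed and those lost to follow-up. The Recruitment section makes contact mainly indirect: "Patients will be the source of help to recruit study participants". It adds posters at the rehabilitation reception and in pharmacies, and a poster and video clip on the University's social media. The section on counterbalancing for confounding and bias says that numbers randomised, numbers lost and reasons for withdrawal will be recorded for each group.

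**Acceptability.** The section on recruitment for interviews states: "From a sample of first-degree relatives who completed the programme, 24 individuals will be asked to participate in the interviews". Selection varies on sex, age and 12-month risk profile, and deliberately includes people who improved and people who did not. That section and Objective 2 give the post-intervention questionnaire to all intervention participants.

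**The concern.** The Discussion gives estimating recruitment and retention rates as one purpose of the pilot, and the Sampling frame section says there are no existing records of uptake or attrition. The pilot is therefore the source of these planning figures.

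A retention percentage on the approached base does not answer the planning question, which is what share of those randomised will still provide data. It moves with how widely the study was advertised, even if nobody behaves differently after randomisation. The base itself is also unclear. If being approached means being exposed to a poster or a post, it cannot be observed. If it means having contacted the team, it is the same as having expressed interest.

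For acceptability, the article's definition includes the difficulties participants met in trying to comply. People who left because of such difficulties are well placed to describe them, and the interview frame leaves them out.

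**Working it through.** **1. The plan's own figure.** Sampling frame gives about 7 ACS admissions a week, about 40% premature, over 52 weeks: 7 × 0.40 × 52 = 145.6 index patients a year. The stated yield of over 100 eligible relatives needs at least 100 / 145.6 = 0.69 eligible relatives per index patient. The article gives no number of relatives per patient, so this shows consistency only. The 146 counts premature ACS admissions. It is an upper limit on patients told about the study, because only those attending rehabilitation are informed there. It is not a count of relatives approached.

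**2. Effect of the base on retention.** Let A be approached, N randomised and R retained. The stated rule gives R/A = (N/A) × (R/N), that is, uptake × retention. N = 100 is the planned sample. R = 80 and the values of A are assumptions.

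| A | Uptake N/A | Stated rule R/A | Retention R/N |
|---|---|---|---|
| 146 | 68% | 55% | 80% |
| 200 | 50% | 40% | 80% |
| 400 | 25% | 20% | 80% |
| 500 | 20% | 16% | 80% |
| 1000 | 10% | 8% | 80% |

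The Wilson 95% interval for 80/100 is 71.1% to 86.7%, whatever A is.

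**3. The two parts cannot be separated from R/A alone.** With 200 approached, 100 randomised and 60 retained, R/A = 0.50 × 0.60 = 30%. With 300 approached, 100 randomised and 90 retained, R/A = 0.333 × 0.90 = 30%. Retention of 60% and of 90% give the same reported figure.

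**4. Consequence for planning.** Sample size is usually inflated by 1/retention. At 80% the factor is 1/0.80 = 1.25. If the 40% from the row A = 200 were taken as retention, it would be 1/0.40 = 2.5, twice as many people to randomise.

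**5. Interview frame.** With 50 allocated to the intervention and an assumed drop-out of 10%, 20% or 30%, the number outside the frame is 5, 10 or 15. Selection on 12-month risk profile points the same way, because a person lost before 12 months has no such profile.

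**The case against.** The strongest reply is that the plan already collects what is needed. The Feasibility list runs from reached to lost to follow-up and names a retention and drop-out rate. The counterbalancing section records numbers randomised and lost in each group. Retained over randomised can therefore be calculated without new data. Agreed over approached is also an ordinary recruitment measure where the approach is countable, and telephone screening is a point at which the route of contact can be asked. All of this stands. It makes the correction cheap, but the sentence that fixes the denominator remains wrong for retention.

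On acceptability, the questionnaire goes to all intervention participants, non-improvers are sampled on purpose, and reasons for withdrawal are recorded. This too stands, as a partial offset. Non-improvers in the frame still completed the programme, and the questionnaire's ruler scales were built to rank components, which does not show why someone left.

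A reader might infer more than the text supports:

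- That both primary outcomes have a wrong denominator. Acceptability has none: purposive interviews with thematic analysis, and scales that rank components, produce no acceptability proportion. For the same reason no percentage bias can be attached to it.
- That uptake and retention from this pilot cannot be used. The recorded counts allow both to be derived on sound bases.
- That the plan lacks progression limits, given the remark "A sample of 100 participants should be adequate to prove that the process is viable". That sentence is sample-size rationale, and a condensed article may leave such limits to the full protocol.

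**Conclusion.** The point holds in two limited parts and should be corrected.

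First, Objective 1 as written puts retention over the number approached. With 80 of 100 retained, the reported figure would be 40% or 16% at 200 or 500 approached, against 80% (95% CI 71% to 87%) of those randomised. The 80 and the approached counts are illustrations, since the article gives no uptake or attrition figures. The confounding of uptake with retention does not depend on them. The missing definition of approached is a further weakness for open and patient-relayed routes.

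Second, the interview frame excludes non-completers, about 5 to 15 of 50 intervention participants if drop-out is 10% to 30% (assumed). This is a restriction of the sampling frame whose effect on the themes cannot be quantified.

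**What to change.** **Feasibility.** Replace the single denominator in Objective 1 with one for each stage, consistent with the Feasibility list and the counterbalancing section:

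- eligible over those who expressed interest or were screened;
- agreed over eligible;
- retained over randomised, by arm, at 6 and 12 months.

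Give each with a 95% CI. Report reach by channel as counts only, without using it as a base. The cost is wording, since these counts are already to be recorded.

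**Acceptability.** Keep 24 interviews, but open the frame to intervention participants who stopped the calls or withdrew and are willing to talk. Non-completers are harder to reach, so some of these places may revert to completers. The report should then say how many were invited and how many took part.

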##### Objective 2: Acceptability

A post-intervention questionnaire, consisting of ruler scales (0–10), was developed to rank the intervention components' order. This data will be collected from all the intervention participants.

The audio-recorded data from the interviews shall be transcribed verbatim by the author. The data will be validated with the study participants and analysed using a thematic analysis method [49]. The phases to be applied are familiarisation with the data and identifying items of interest, code generation, management of the coding process, reviewing potential themes, defining and labelling the themes, and producing a report [49].

#### Secondary outcome analysis

##### Objective 3: Estimates of effect and preliminary evidence of efficacy

The likely range of effects will be estimated using liberal confidence intervals. Preliminary estimates of intervention efficacy will be established via hypothesis tests with liberal alpha values (e.g. 0.15, 0.2). Numerical outcomes measured on an interval level, and numerical outcomes measured on an ordinal scale that can be considered approximate to interval level, will be assessed using independent samples t tests. Categorical data will be assessed using the chi-squared test for association.

Intention-to-treat analysis will be used to test for the differences between the two groups at the endpoint [50]. Intention-to-treat analysis is considered the gold standard method for evaluating a new intervention. This method includes all study participants whether or not they have completed the study program and will preserve the randomisation process as it keeps the groups balanced in their number of participants in case of any drop-outs, thus minimising biases [51].

Risk ratios (RRs) will be generated for selected outcome variables, dichotomised as necessary, from proportions of participants meeting particular criteria (e.g. control of blood pressure) in the control and intervention groups.

Effect sizes such as Cohen's d statistics will be calculated for each outcome measure and presented alongside parameter estimates in each group and associated confidence intervals. These, in conjunction with other statistics derived from the pilot analysis, may be used to estimate sample size for a subsequent follow-up RCT [38].

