**Discussion:**

Preventive cardiology guidelines highlighted the importance of lifestyle interventions, and lifestyle intervention adherence was proven to reduce atherosclerotic cardiovascular disease (ASCVD) risk, regardless of the individual's genetic risk. Preventive cardiology programmes may fail to adequately support persons in modifying risky behaviours, and research demonstrates that healthy practices among high-risk individuals can remain suboptimal.

Siblings and offspring of patients with premature CHD are at increased risk of ASCVD. Despite this, there is no process in place for routine screening and support to modify risk. It is hypothesised that participants assigned to the intervention arm will show more cardio-protective lifestyle-related improvement from the baseline than those in the control group. To date, this is the first trial being conducted amongst Maltese first-degree relatives. This study addresses the needed research, and the results will inform a definitive trial.

The funding institution is the University of Malta.

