## Aim and objectives

This study aims to evaluate a pilot study of a preventive cardiology program designed to promote risk reduction in a sample of asymptomatic first-degree relatives of patients with premature CHD.

Primary objectives are as follows:
Feasibility: To assess the recruitment processes and study uptake to inform the feasibility of a large-scale randomised controlled trialAcceptability: To determine whether the Intervention for risk reduction is acceptable by first-degree relatives

Secondary objectives are as follows:
3.Potential effectiveness: To determine if the programme provides preliminary evidence for modifying lifestyle behaviours; physiological, anthropometric, biochemical parameters; Heart Age (estimated age based on ASCVD risk); and health literacy4.Association between variables: To determine if the programme provides preliminary evidence for an association with lifestyle factors such as Mediterranean diet and physical activity, which themselves can act as determinants to clinical outcomes such as BMI/WC/lipids/blood pressure/HbA1c.

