### Secondary outcomes

#### Potential intervention effectiveness

Preliminary evidence for the effect of the intervention will be determined by an increase in the mean smoking cessation attempts, increased mean Mediterranean diet score, and physical activity level. A decrease in the mean serum lipids, blood pressure level, waist circumference, and body mass index, and Heart Age will be considered as improvements in cardiovascular risk factors if statistically significant. Any trends identified across variable results will be explored.

The following are secondary outcome measurements considered:
Smoking status

Smoking status will be answered by a 'yes' or 'no.' As self-reporting depends on participants' honesty, those who report that they have stopped smoking will be tested for expired carbon monoxide using a carbon monoxide monitor.
Mediterranean diet score

The 14-point Mediterranean Diet Adherence Screener (MEDAS) [33] is a fourteen-item questionnaire that assesses adherence to the Mediterranean diet with two 'yes-or-no' questions on food intake habits and another twelve questions on food consumption frequency. The questionnaire is based on the nine-item index used in the PREDIMED study, and it covers the use of Mediterranean diet habits and frequency of consumption of Mediterranean food items. If the item/question is not met, a score of zero will be recorded. Therefore, the final score will range from 0 to 14. The higher the score, the greater the adherence to the Mediterranean diet.
Physical activity level

The rapid assessment of physical activity (RAPA) questionnaire is a 9-item valid questionnaire, which requires 2 to 5 min to complete [34]. The questionnaire is based on the Centres for Disease Control and Prevention (CDC) guidelines, suggesting a minimum of 30 min of moderate physical activity daily. The questionnaire covers a range of physical activity levels, from sedentary to regular vigorous physical activity and strength training and flexibility. The total score of the first seven items is one score for each and, thus, scoring is from 0 to 7 points. Responses to strength training and flexibility items are scored separately, with strength training = 1 point, flexibility = 2 points, or both = 3 points. Therefore, the final score would range from 0 to 10.
Biochemical measures

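### Five risk factors are to be called improved when a test is significant, but the significance level is left open at a liberal value and no multiplicity control is stated

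*Protocol article*

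**What the plan says.** Three parts of the Protocol article bear on this.

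- *Potential intervention effectiveness* (Secondary outcomes) has two sentences with different rules. Preliminary evidence of effect "will be determined by an increase in the mean smoking cessation attempts, increased mean Mediterranean diet score, and physical activity level"; this sentence sets no significance condition. Decreases in serum lipids, blood pressure, waist circumference, body mass index and Heart Age "will be considered as improvements in cardiovascular risk factors if statistically significant". The significance rule therefore covers five domains, and the section names eight in all.
- *Objective 3: Estimates of effect and preliminary evidence of efficacy* gives the tests and the level: "Preliminary estimates of intervention efficacy will be established via hypothesis tests with liberal alpha values (e.g. 0.15, 0.2". Numerical outcomes "will be assessed using independent samples t tests". Sidedness is not stated. The group comparison is made at the endpoint, in the singular. The same section plans liberal confidence intervals, without a level, and effect sizes for each outcome.
- *Sampling frame* justifies the 100 participants on feasibility grounds: "As the pilot study is not expected to be powered to detect differences between groups".

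The direction of interest is clear from the abstract's *Discussion*: "participants assigned to the intervention arm will show more cardio-protective lifestyle-related improvement from the baseline than those in the control group".

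**The concern.** The protocol makes a hypothesis test the arbiter of whether a risk factor improved, and then does not say where the line is. A result with p = 0.17 is an improvement at alpha 0.2 and not at 0.15, and nothing in the text prevents the choice being made after the data are seen. The test is applied to several outcomes, with no stated allowance for that, in a study that disclaims power for group comparisons.

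What is at stake is the secondary conclusion on preliminary efficacy. A programme that does nothing could be reported as having improved a cardiovascular risk factor because one of several outcomes crossed a loose line. The word improvement in a published pilot will carry more weight than a test at alpha 0.2 can bear.

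**Working it through.** The protocol states no power, familywise error or effect-based sample size, so there is no figure to reproduce. The check is how often the stated rule would credit an ineffective programme.

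**Inputs from the protocol**
- Alpha: 0.15 or 0.2, both given as examples (*Objective 3*).
- Domains under the significance rule: 5 (*Potential intervention effectiveness*).
- Domains named in that section: 5 + 3 = 8. Using all eight assumes that the three behavioural outcomes are tested in the same way.
- One time point, because the comparison is at the endpoint.

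**Assumptions, because the protocol does not give them**
- No true effect, and one test per domain.
- Two-sided tests as the main case and one-sided as the alternative.
- Equal correlation between test statistics of 0, 0.3 or 0.5.

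Some correlation is plausible: *Heart Age* is calculated from, among other things, systolic pressure, cholesterol, weight and height, and body mass index uses the same weight and height.

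**Formula under independence.** Only a favourable significant result counts as an improvement. With two-sided tests its probability per domain is alpha/2, so over k domains

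P(at least one false favourable verdict) = 1 − (1 − alpha/2)^k.

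With one-sided tests in the favourable direction, alpha replaces alpha/2.

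*Two-sided*
- k = 5: 1 − 0.925^5 = 0.323 (alpha 0.15); 1 − 0.9^5 = 0.410 (alpha 0.2)
- k = 8: 1 − 0.925^8 = 0.464; 1 − 0.9^8 = 0.570

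*One-sided*
- k = 5: 1 − 0.85^5 = 0.556; 1 − 0.8^5 = 0.672
- k = 8: 1 − 0.85^8 = 0.728; 1 − 0.8^8 = 0.832

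**Under correlation**, by simulation of equicorrelated normal statistics (400,000 draws). The first figure in each cell is alpha 0.15, the second alpha 0.2.

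| Domains | Tests | Correlation 0 | 0.3 | 0.5 |
|---|---|---|---|---|
| 5 | two-sided | 32%, 41% | 27%, 34% | 23%, 29% |
| 8 | two-sided | 46%, 57% | 36%, 44% | 30%, 37% |
| 5 | one-sided | 56%, 67% | 46%, 56% | 40%, 49% |
| 8 | one-sided | 73%, 83% | 58%, 67% | 48%, 58% |

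The expected number of false favourable verdicts over the five domains, two-sided, is 5 × 0.075 = 0.375 at alpha 0.15 and 5 × 0.1 = 0.5 at alpha 0.2. These expectations do not depend on the correlation.

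**The case against.** The best defence is that this is a pilot and says so. The efficacy objective is secondary and labelled preliminary, and a liberal alpha is a deliberate trade of false positives for sensitivity. The trade buys something: with 50 per group and an assumed standardised difference of 0.3, the normal approximation Φ(0.3 × √25 − z) gives power of 32% at two-sided alpha 0.05, 52% at 0.15 and 59% at 0.2. Estimates, intervals and effect sizes are already planned for each outcome, and details of alpha and multiplicity may sit in a full protocol or analysis plan that is not shown.

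Most of this stands. A declared liberal alpha is acceptable in itself, and running tests in an unpowered pilot does not contradict *Sampling frame*. What it does not answer is that the article itself turns significance into a verdict of improvement while leaving the level open. That is a rule stated and fixed badly, not a detail left out.

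Several stronger readings are tempting and are not supported:

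- *An ineffective programme would probably be credited with an improvement.* With two-sided tests the chance stays below one half for the five domains throughout, and for eight domains once the correlation is 0.3 or more.
- *The significance rule covers all eight domains.* It covers five. The three behavioural outcomes are in a sentence without that condition.
- *Two follow-ups double the testing.* Measurements are taken at 6 and 12 months, but *Objective 3* tests at the endpoint only.
- *There are many more tests, and a fall in HDL cholesterol would be praised.* The lipid fractions are not listed, so both points rest on guesses about the panel.
- *The next trial would be built on false positives.* *Future research opportunities* makes the large trial depend on feasibility, and *Objective 3* calculates effect sizes for every outcome, not only for significant ones.

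**Conclusion.** The concern holds in a limited form. The protocol declares improvement in five risk-factor domains by statistical significance, at a level given only by example and with no multiplicity control stated, in a pilot not expected to be powered. With two-sided tests and no effect, the chance of at least one false favourable verdict is 32% to 41% over the five domains if independent and about 23% to 29% at correlation 0.5. For eight domains, if all were tested, it is 46% to 57% and about 30% to 37%. One-sided tests raise the ranges to 40% to 67% and 48% to 83% over correlations from 0.5 to 0.

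The sidedness, the correlations, one test per domain and the testing of the three behavioural outcomes are assumptions. The fault lies in the significance-based verdict, not in the liberal level alone. It touches the preliminary-efficacy conclusion; it does not touch the feasibility and acceptability objectives or the decision to go on to a larger trial.

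**What to change.** Two changes of wording:

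1. In *Potential intervention effectiveness*, delete statistical significance as the criterion for calling a change an improvement.
2. In *Objective 3*, replace the hypothesis-test verdict based on unadjusted t tests with the baseline-adjusted between-arm difference at 12 months for every outcome. Give each with a confidence interval at one level fixed in advance, describe the results as preliminary, and make no claim of efficacy. An interval that excludes zero should not be read as a verdict, or the same rule returns under another name.

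The cost is close to nil, because baseline and 12-month measurements, intervals and effect sizes are already planned. The downside is that the pilot will have no significant results to quote.

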**Methods/design:**

We are conducting a 12-month single-centre, two-armed group randomised controlled trial (RCT), recruiting a sample of 100 asymptomatic first-degree relatives of patients with premature coronary heart disease (CHD). The study seeks to test an evidence-based intervention to reduce modifiable risk and determine its feasibility and acceptability. The Intervention will be delivered at an outpatient office based in a large acute academic hospital. It will comprise risk communication using an online risk calculator, a counselling style adapted from motivational interviewing, and 12 weekly telephone goal reinforcement calls (3 months). Control subjects will receive verbal lifestyle advice only. Feasibility will be assessed through recruitment and retention. Qualitative evaluation interviews will be conducted with a subsample of 24 purposefully selected participants at 12 months. Assessment for risk factor changes will be measured at pre-intervention and 6 and 12 months. Associations between variables will also be assessed descriptively.

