### Materials

#### Sociodemographic questionnaire

A questionnaire was designed to collect sociodemographic data, including questions on age, sex, educational level, employment status, time of the patient coronary event, and whether participants live alone or live with others. These variables will be collected to characterise the sample. However, as randomisation is not guaranteed to result in perfectly balanced groups at baseline, variables that may be associated with the outcome will be checked for balance and controlled for in subsequent analysis if necessary.

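### Numerical risk-factor outcomes are compared by endpoint t tests that leave out the baseline value the trial collects, which is valid but gives up precision

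*Protocol article*

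**What the plan says.** The section on Objective 3 (estimates of effect and preliminary evidence of efficacy) names one method for interval-level or near-interval outcomes: they "will be assessed using independent samples t tests". It then gives the contrast: "Intention-to-treat analysis will be used to test for the differences between the two groups at the endpoint". It mentions no baseline value, change score or covariate. Cohen's d and liberal confidence intervals are to be reported, and the section says these statistics may help to size a follow-up RCT.

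The baseline data exist. The abstract's methods paragraph says "Assessment for risk factor changes will be measured at pre-intervention and 6 and 12 months", and the Follow-up section lists "baseline/pre-intervention, 6 months, and 12 months after baseline/pre-intervention". The abstract's discussion states the hypothesis in terms of change: "participants assigned to the intervention arm will show more cardio-protective lifestyle-related improvement from the baseline than those in the control group".

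The Sociodemographic questionnaire section contains the only provision for adjustment: "variables that may be associated with the outcome will be checked for balance and controlled for in subsequent analysis if necessary". It does not name the variables, the trigger or the model, and the Objective 3 section does not take it up. The section on counterbalancing for confounding factors and bias adds that allocation is not stratified.

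**The concern.** Risk factors such as blood pressure, lipids, waist circumference and BMI usually correlate within a person over a year, so the baseline value explains part of the spread at 12 months. A t test on endpoint values leaves that spread in the standard error. The intervals are then wider than the collected data require.

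The balance-check rule does not repair this. If it is not triggered, no precision is recovered. If it is triggered, the model has been chosen after looking at the data, and the named test has no place for a covariate. The rule also does not mention the baseline value of the outcome, which is the natural first covariate.

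What is at stake is the quality of the effect estimates handed to the next trial. The primary objectives of feasibility and acceptability are not affected.

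**Working it through.** **Inputs from the protocol article.** 50 participants per arm (Group randomisation); independent samples t test at the endpoint, with an alpha of 0.20 as one of two examples (Objective 3); no stratification (section on counterbalancing for confounding factors and bias).

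**Assumptions.** The article gives no baseline-to-12-month correlation r, so 0.3 to 0.8 is shown. The SD is taken as equal at both times, tests as two-sided, and all 100 participants as measured.

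**The plan's own figure.** The target of 100 rests on feasibility. No effect size, SD or power is given, so there is no calculation to reproduce.

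**Step 1: endpoint t test.** SE = SD × √(2/50) = 0.200 SD. The 80% half-width is 1.282 × 0.200 = 0.256 SD, about 0.26.

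**Step 2: adjustment for baseline (ANCOVA).** The variance is multiplied by 1 − r², so the saving is r². The n per arm that the t test would need for equal precision is 50/(1 − r²).

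| r | Variance factor 1 − r² | Saving r² | SE (SD) | 80% half-width (SD) | Equivalent n per arm, t test |
|---|---|---|---|---|---|
| 0.3 | 0.91 | 9% | 0.191 | 0.24 | 55 |
| 0.5 | 0.75 | 25% | 0.173 | 0.22 | 67 |
| 0.7 | 0.51 | 49% | 0.143 | 0.18 | 98 |
| 0.8 | 0.36 | 64% | 0.120 | 0.15 | 139 |

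Estimating the slope costs a variance factor of about 1 + 1/96, or roughly 1%, which does not alter the picture.

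**Step 3: if change scores were meant.** The variance factor is 2(1 − r): 1.4, 1.0, 0.6 and 0.4. The ratio of ANCOVA to change score is (1 − r²)/[2(1 − r)] = (1 + r)/2: 0.65, 0.75, 0.85 and 0.90. The further saving is therefore 35%, 25%, 15% and 10%. At r = 0.3 a change score is worse than the endpoint t test (SE 0.237 against 0.200 SD), and at 0.5 it is equal.

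**Step 4: chance imbalance.** The baseline difference also has an SE of 0.200 SD. P(|difference| > 0.2 SD) = 2[1 − Φ(1)] = 0.317. P(|difference| > 0.3 SD) = 2[1 − Φ(1.5)] = 0.134. Given a baseline difference b, the expected endpoint contrast moves by r × b. At r = 0.7, a difference above 0.2 SD moves it by at least 0.7 × 0.2 = 0.14 SD.

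**Step 5: check by simulation.** In 20,000 simulated trials without an effect for each r, the endpoint t test at nominal 0.20 rejected in about 20% overall. Among trials with a baseline difference above 0.3 SD, it rejected in 24%, 36%, 54% and 65% at r = 0.3, 0.5, 0.7 and 0.8. The test is correct on average, but misleading in the trials that happen to be imbalanced.

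**The case against.** Several points on the other side have force.

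- **A reader might infer that imbalance is simply left in the estimate.** The sociodemographic section does foresee some control for it. The fair criticism is that the rule is vague, depends on the data and cannot be carried out with the named test.
- **A reader might infer that the endpoint contrast is biased.** It is not. Over randomisation it is unbiased with the correct overall error rate. The 0.14 SD is a shift conditional on an observed imbalance.
- **A reader might infer that the analysis contradicts the hypothesis about improvement.** Under randomisation, the endpoint difference and the difference in change have the same expected value. The issue is efficiency.
- **The t test might be meant for change scores.** The text never says which values enter it, and the abstract speaks of changes. The raw-endpoint reading is the more natural, but the larger savings depend on it; Step 3 gives the smaller ones.
- **Not every outcome is known to have a baseline value.** The table of data collection points is not shown, and the number of smoking cessation attempts is not clearly a baseline measure. Nor does the article support a claim that age accounts for most of the spread in Heart Age; it only lists age among the inputs.
- **Covariates and models are often left to a fuller document.** That excuses silence, but here the article commits to a specific test and contrast.

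The secondary, preliminary status of these outcomes stands and limits the weight of the point. None of this removes the loss of precision, which is present for any non-zero correlation apart from the roughly 1% cost of estimating the slope.

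**Conclusion.** The point holds as one of efficiency and prespecification, not of validity. The named analysis omits a baseline value that the trial collects for its risk factors, and the conditional balance rule neither restores the precision nor fits a t test. The variance given up ranges from 9% to 64% against a raw endpoint t test for r from 0.3 to 0.8, and from 35% to 10% if change scores were intended. A baseline difference above 0.2 SD can be expected in about 32% of trials for any one outcome.

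These sizes rest on the assumed correlations, equal SDs and no dropout. The change is worth making because the effect sizes may feed the next trial's sample size. It is not critical, because the pilot is not powered for group differences and its primary objectives lie elsewhere.

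**What to change.** In the Objective 3 section, replace the t test for each numerical risk-factor outcome that has a baseline measurement by linear regression (ANCOVA) of the 12-month value on arm and that outcome's own baseline value. Report the adjusted difference with its liberal confidence interval, and the baseline-to-follow-up correlation, which the later trial will need for its own sample size.

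In the Sociodemographic questionnaire section, replace the balance-triggered rule with covariates fixed in advance. Covariates beyond the baseline value, such as age and sex, are optional.

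The cost is a change of wording before analysis. No new data, visits or participants are needed.
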